#### Exclusion Criteria

Allergy to component of Remimazolam besylate for injection;Woman in gestation and lactation period;Enrolled in other clinical trials in recent 3 months;Patients who needs deep sedation levels (RASS < −2) based on clinical considerations;Other circumstance that identified by researchers that do not suitable for this clinical trial.

## Interventions

Patients will be randomized as soon as they arrive at intensive care unit, the end point of this study is 28 days after patients depart from intensive care unit.

### Experimental Group: Remimazolam Besylate

Patients should be given study drugs after randomization. Syringe pump is used to administer medication. Loading dose of Remimazolam is 0.02–0.1 mg/kg, which is administered for <1 min initially. Maintaining dose is 0.2–1 mg/kg/h. Sedative target is RASS between 0 and −2 points. Excepts for fentanyl and Remimazolam, no analgesic or sedative could be used during the experimental time period.

### Positive Control Group: Propofol

Patients should be given study drugs after randomization. Syringe pump is used to administer medication. Loading dose of propofol is 0.2 mg/kg, which is administered for <1 min initially. Maintaining dose is 0.3–4.0 mg/kg/h. Sedative target is RASS between 0 and −2 points. Excepts for fentanyl and propofol, no analgesic or sedative could be used during the experimental time period.

### Rescue Therapy for Experimental Group

During the treatment of the experimental group, if the RASS cannot be maintained at 0 to −2 points at the maximum Remimazolam maintenance dose of 1 mg/kg/h for more than 3 min, a loading dose of propofol (0.2 mg/kg) can be given intravenously. If RASS fails to satisfy after three loading doses of propofol, Remimazolam is discarded and 0.3–4.0 mg/kg/h of propofol are used as rescue therapy for experimental group.

## Outcomes

### Primary Outcomes

Validity endpoint is satisfaction rate of sedation, which equals to proportion of time in target sedation range (RASS score, 0 to −3) without use of rescue therapy of the total duration of study drug infusion. Safety endpoint is the incidence of hypotension (SBP < 90 mmHg), the incidence of hypoxia (SpO_2_ < 90%), and the incidence of bradycardia (HR < 75% baseline HR or HR < 50 bpm).

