### Secondary Outcomes

For validity evaluation, the secondary outcome includes incidence of delirium (subjects with delirium/total number of subjects × 100%) by 12 and 24 h after entering ICU. Time to weaning and extubation are recorded. Difficulty of nursing is evaluated by TISS-28 scoring system. RASS, BIS and PI are recorded every 30 min during medications. For safety evaluation, the secondary outcome includes 28-days survival, vital signs during medications, total dose and dose per kilogram body weight of analgesic and sedatives and incidence of rescue therapy in experimental group, side-effect report from usage of medications to 28 days after patients depart from intensive care unit. Side-effect is defined as hypotension, bradycardia, elevation of bilirubin, abnormal urine (Elevated urinary leucocyte/ketone body/bilirubin) in this study.

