## Sample Size Planning

In this study, propofol was used as a positive control. The hypothesis is compared with propofol, Remimazolam Besylate for Injection has non-inferiority satisfied rate of sedation on ERAS patients under mechanical ventilation in ICU. Setting inspection level: α = 0.05, 1–β = 80%, the non-inferiority threshold is 10%. Subjects in experimental group and control group is 1:1. According to the results of previous clinical trials, the target sedation rate of the propofol group is 82% (11), assuming that the target sedation rate of the Remimazolam Besylate group is 92%, a total of 70 subjects (35 for experimental group and 35 for control group each) should be enrolled to meet inspection level. Sample size calculations allow for 15% loss of cases, a total of 84 subjects (42 for experimental group and 42 for control group each) are enrolled in this clinical trial.

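### The primary endpoint scores RASS 0 to −3 as on target, but both arms are titrated to RASS 0 to −2

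*Protocol article*

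**What the plan says.** Primary Outcomes defines the efficacy endpoint, the satisfaction rate of sedation, as the "proportion of time in target sedation range (RASS score, 0 to −3) without use of rescue therapy", divided by the total duration of study drug infusion.

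Four other places use −2 as the lower limit:

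- Experimental Group: "Maintaining dose is 0.2–1 mg/kg/h. Sedative target is RASS between 0 and −2 points".
- Positive Control Group: "Maintaining dose is 0.3–4.0 mg/kg/h. Sedative target is RASS between 0 and −2 points".
- Rescue Therapy for Experimental Group: rescue applies "if the RASS cannot be maintained at 0 to −2 points at the maximum Remimazolam maintenance dose".
- Exclusion Criteria rule out "Patients who needs deep sedation levels (RASS < −2) based on clinical considerations".

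Sample Size Planning builds the non-inferiority test on this endpoint. It states that "the target sedation rate of the propofol group is 82" percent and assumes 92% for remimazolam, with a 10% margin. It does not say which RASS range these rates refer to. Secondary Outcomes states that "RASS, BIS and PI are recorded every 30 min during medications".

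**The concern.** Both ranges are called the target, and they differ by one RASS level. Staff are told to keep patients between 0 and −2. A patient who drifts to −3 has missed that instruction, yet the time counts as success. The extra level lies only on the deep side: one level of over-sedation is credited and no under-sedation is.

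The endpoint carries the non-inferiority claim. The arms receive different drugs under different dosing rules, and only the remimazolam arm has a rescue rule, so equal time at −3 cannot be taken for granted. More time at −3 on remimazolam would move the comparison towards non-inferiority point for point. More on propofol would move it the other way. Equal time would leave the difference unchanged.

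The document also supports two versions of the primary result. Switching from one to the other once data have been seen would be open to challenge, particularly in a trial whose title calls it open-label.

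**Working it through.** **1. The ranges side by side**

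| Section of the protocol article | RASS range | Use |
|---|---|---|
| Experimental Group | 0 to −2 | titration target |
| Positive Control Group | 0 to −2 | titration target |
| Rescue Therapy | 0 to −2 | rescue trigger |
| Exclusion Criteria | below −2 is deep sedation | patient selection |
| Primary Outcomes | 0 to −3 | scored as success |

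The direct conflict is between the two dosing sections and Primary Outcomes. The rescue rule mainly concerns under-sedation and is listed only for its range. No section reconciles the two ranges.

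**2. The plan's own sample size**

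Inputs from Sample Size Planning: 82% propofol, 92% remimazolam, margin 10 points, α = 0.05, power 80%. The section does not say whether α is one-sided; one-sided 0.05 reproduces its figure.

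n per arm = (1.645 + 0.842)² × [pP(1 − pP) + pR(1 − pR)] / (pR − pP + 0.10)²

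= 6.185 × (0.1476 + 0.0736) / 0.20² = 34.2, rounded up to 35. Then 35 / 0.85 = 41.2, rounded up to 42 per arm, or 84 in total. Both stated figures are reproduced.

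**3. What a difference in time at −3 could do (illustration)**

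Assumptions: rates treated as binary, as in the plan's formula; 35 per arm; one-sided α of 0.05. The excesses of 5 and 10 points are chosen for illustration and do not come from the documents.

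Chance of declaring non-inferiority = Φ[(pR − pP + 0.10) / √(pR(1 − pR)/35 + pP(1 − pP)/35) − 1.645]

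Suppose the true rates on 0 to −2 are 72% remimazolam and 82% propofol, exactly at the margin:

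| Excess at −3 | Scored rates, remimazolam vs propofol | Chance of declaring non-inferiority |
|---|---|---|
| none | 72 vs 82 | 5.0% |
| remimazolam +5 | 77 vs 82 | Φ(0.05/0.0963 − 1.645) = 13.0% |
| remimazolam +10 | 82 vs 82 | Φ(0.10/0.0918 − 1.645) = 28.9% |
| propofol +5 | 72 vs 87 | 1.5% |
| propofol +10 | 72 vs 92 | 0.3% |
| both +5, or both +10 | 77 vs 87, or 82 vs 92 | 5.0% |

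Exact enumeration of the same Wald rule gives similar values for a remimazolam excess of 0, 5 and 10 points: about 0.057, 0.145 and 0.309.

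Suppose instead that the true rates on 0 to −2 are the plan's 92% and 82%:

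| Excess at −3 | Scored rates, remimazolam vs propofol | Power |
|---|---|---|
| none | 92 vs 82 | Φ(0.20/0.0795 − 1.645) = 80.8% |
| propofol +5 | 92 vs 87 | 65.9% |
| propofol +10 | 92 vs 92 | 45.9% |

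**4. Weight of one reading in one patient**

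The infusion length is not stated, and Primary Outcomes does not say how time in range is derived. If it comes from the 30-minute readings, infusions of 10, 12 or 24 h give 20, 24 or 48 readings. One reading at −3 then moves that patient's score by 1/20 = 5.0, 1/24 = 4.2 or 1/48 = 2.1 points.

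**The case against.** The strongest reply is that the wider band may be a deliberate tolerance: titrate to a narrow range and score a slightly wider one. On that reading the endpoint is already prespecified, nothing has to be chosen after the data are seen, and the 13% and 29% are not false positives, because 0 to −3 is the intended measure. This has some force against the post hoc argument and against reading the first scenario as error inflation. It does not remove the conflict. Primary Outcomes does not describe a tolerance; it uses the word target for a range that the dosing sections define differently, and it widens only the deep side.

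A second objection is that the figures model a binary outcome, while the endpoint is a proportion of time in each patient. That is correct. With an assumed between-patient SD of 20 points and 35 per arm, the standard error of the difference is 0.20 × √(2/35) = 0.0478. A remimazolam excess of 5 points at the margin then gives Φ(0.05/0.0478 − 1.645), about 27% and not 13%. At the planning rates, a propofol excess of 5 points leaves power at Φ(0.15/0.0478 − 1.645), about 93% and not 66%. The figures could be off in either direction and should be read as illustrations only.

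Three smaller points also stand. No document shows any difference in time at −3, so bias is possible but not demonstrated. The source of the 82% is not available here, so its range cannot be settled. The Allocation section says that those assessing, recording and analysing are blinded, which softens the open-label argument, although it sits awkwardly with the title.

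**Conclusion.** The concern holds. The primary efficacy endpoint, as written, conflicts with the sedation target that both arms are instructed to follow, and one level of over-sedation is scored as success in the 10-point non-inferiority comparison. This is a conflict in the stated text, not detail left to a fuller document. It should be settled before enrolment.

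The effect cannot be sized from the documents because time at −3 is not given for either arm. It could be nil if the arms are equal. The illustrated shifts (from 5% to 13% or 29% at the margin, or power falling from 81% to 66% or 46%) rest on the assumed excesses of 5 and 10 points, a binary outcome, 35 per arm and one-sided α of 0.05. The need to correct the text does not depend on them. The sample size arithmetic itself is sound.

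**What to change.** Amend Primary Outcomes so that the satisfaction rate is scored on RASS 0 to −2. If the clinical team does intend 0 to −3, change the two dosing sections, the rescue rule and the exclusion criterion to match. Report the other range as a prespecified sensitivity analysis, and tabulate time above, within and below target by arm. In Sample Size Planning, state which range the 82% and 92% refer to, and recheck the sample size if it is not the one chosen.

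The change is one line in the endpoint definition and its programming. RASS is already recorded, so no new data are needed. The possible cost is in numbers, because the rate on 0 to −2 cannot exceed the rate on 0 to −3. If 82% and 92% were defined on 0 to −3 and both fell by the same amount (an assumption), the plan's formula gives:

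- 5 points lower (77% vs 87%): 6.185 × 0.2902 / 0.04 = 44.9, so 45 evaluable per arm, or 45 / 0.85 = 52.9, that is 53 enrolled per arm.
- 10 points lower (72% vs 82%): 6.185 × 0.3492 / 0.04 = 54.0, so 54 evaluable per arm, or 54 / 0.85 = 63.5, that is 64 enrolled per arm.

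The plan has 35 evaluable and 42 enrolled per arm. These figures share the binary assumption.

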### Eligibility Criteria

#### Inclusion Criteria

Meet criteria of enhanced recovery after surgery (ERAS);Mechanical ventilated when enrolled and have estimation of more than 10 h of mechanical ventilation in ICU;Aged between 18–75 years old and 18 ≤ BMI ≤ 30 kg/m^2^;Clearly know the purpose and objective of this clinical study and voluntarily enrolled.

Criteria of ERAS: (1) without dysfunction of nervous system or Glasgow Coma Score >12; (2) a satisfied glucose level (random blood glucose <11.1 mmol/L during screening stage) for diabetes mellitus patients; (3) Without acute coronary syndrome in recent 6 months; (4) Without bradycardia and third-degree atrioventricular block (except for patients with pacemaker) during screening stage; (5) systolic blood pressure >90 mmHg with no usage of vasoactive agent during screening stage; (6) without mental illness (schizophrenia, depressive disorder), cognitive dysfunction (identified by MMSE), epilepsy, history of abuse of psychotropic, or anesthesia medication; (7) without disorder of coagulation function (PT/INR/APTT > 1.5 × upper limit), bleeding tendency (active peptic ulcer), under treatment of thrombolysis and anticoagulant; (8) without disorder of liver function (ALT/AST > 2 × upper limit and total bilirubin > 1.5 × upper limit); (9) without disorder of renal function (Creatine or BUN/Urea > 1.5 × upper limit); without dialysis patients.

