## Data Management

Data will be collected using an online data collection form via a secure, password-protected platform with predefined data fields. Based on the PUMC Intensive Care Medical Information System and Database (PICMISD), all bedside instruments, including monitors, mechanical ventilators, and blood gas analyzers are connected into a central server to achieve real-time data acquisition and synchronization. The clinical data of the patients involved in this study included (1) monitors parameters: respiratory rate (RR), heart rate (HR), mean arterial pressure (MAP), body temperature, central venous pressure (CVP), perfusion index (PI), bispectral index (BIS). (2) Data of arterial blood gas analysis (ABG), including lactate level, pO2, GAP, ScvO_2_. (3) Data of Biochemical laboratory analysis and evaluation scale. (4) Medication: usage and drip speed of vasoactive agent, liquid usage and balance, usage and drip speed of sedatives and analgesics. All data used in the statistical analyses were collected during the clinical trial. All identifiable data collected, processed and stored for the purposes of the project will be kept confidential at all times and comply with Good Clinical Practice guidelines for Research and the General Data Protection Regulation. The research project will be monitored closely by a certified external auditor to ensure that study activities are carried out in accordance with the protocol, good clinical practice and applicable regulatory requirements. Data quality will also be audited.

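### The primary efficacy endpoint divides by study drug infusion time, so an experimental patient switched to rescue propofol is scored only on the period before the switch

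*Protocol article*

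**What the plan says.** Under Primary Outcomes, the article defines the efficacy endpoint as the share of time in the target RASS range "without use of rescue therapy of the total duration of study drug infusion". The clause on rescue limits the numerator; the infusion time is the denominator.

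The section on the experimental group says "Patients should be given study drugs after randomization" and then describes remimazolam dosing. The section on rescue for that group sets out the steps when RASS cannot be held at the maximum maintenance dose: propofol loading doses and, if three of them fail, "Remimazolam is discarded and 0.3–4.0 mg/kg/h of propofol are used as rescue therapy for experimental group".

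The propofol section describes no rescue and says "Excepts for fentanyl and propofol, no analgesic or sedative could be used during the experimental time period". Secondary Outcomes lists the incidence of rescue for the experimental group only.

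Sample Size Planning sets up a non-inferiority comparison of this endpoint: "the target sedation rate of the propofol group is 82" per cent, the remimazolam rate is assumed to be 92%, and "the non-inferiority threshold is 10" per cent.

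**The concern.** Being taken off remimazolam and put on the comparator is the clearest way for remimazolam to fail. The endpoint evidently means rescue to count against the drug, because rescued time is kept out of the numerator. That works while remimazolam is still running and propofol loading doses are given on top. It stops working at the switch: once remimazolam is discarded its infusion time ends, and the remaining hours leave the denominator as well as the numerator. The most serious form of rescue is the one that the score no longer sees.

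The exit is defined in one arm only. In a non-inferiority trial, a rule that can raise only the experimental score makes it easier to conclude that remimazolam is no worse.

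**Working it through.** **The plan's own figure.** With rates of 82% and 92%, a margin of 10 points, one-sided 5% and 80% power:

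n = (1.645 + 0.8416)² × (0.82 × 0.18 + 0.92 × 0.08) / (0.92 − 0.82 + 0.10)² = 6.183 × 0.2212 / 0.04 = 34.2, so 35 per arm.

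35 / 0.85 = 41.2, so 42 per arm and 84 in total. Both figures match the article. One-sided 2.5% gives 44 per arm and does not match. The arm size of 42 and the 10-point margin are carried forward.

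**Direction.** Let *a* be in-target, unrescued time before the switch, *T* the time of the switch and *S* the whole sedation period.

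- As written: a / T.
- Whole period, with time after the switch counted as not satisfactory: a / S.

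Since T ≤ S, a / T is never below a / S. The difference is zero only if a = 0 or T = S.

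**Inputs for the illustration.**

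- S = 600 min. This is an assumption, guided by the inclusion criterion that patients "have estimation of more than 10 h of mechanical ventilation in ICU".
- 12 min out of target before the switch. This is also an assumption: 3 min before the first loading dose (the article's threshold is more than 3 min) plus 3 min after each of three failed doses.
- The time and frequency of switching are not given, so both are varied.

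**Score of one switched patient.**

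| Switch at | As written, (T − 12) / T | Whole period, (T − 12) / 600 | Gap (points) | Gap / 42 (points) |
|---|---|---|---|---|
| 1 h | 48/60 = 80% | 48/600 = 8% | 72 | 1.7 |
| 2 h | 108/120 = 90% | 108/600 = 18% | 72 | 1.7 |
| 5 h | 288/300 = 96% | 288/600 = 48% | 48 | 1.1 |
| 8 h | 468/480 = 97.5% | 468/600 = 78% | 19.5 | 0.5 |

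The last column is the shift in the experimental arm mean from one switched patient among 42.

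**Several switched patients (shift = gap × k / 42).**

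| Number switched, k | Switch at 2 h | Switch at 8 h |
|---|---|---|
| 1 | 1.7 | 0.5 |
| 2 | 3.4 | 0.9 |
| 4 | 6.9 | 1.9 |
| 6 | 10.3 | 2.8 |

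**Sensitivity to the 12 min.** With 30 min lost before the switch, a switch at 2 h scores 90/120 = 75% as written and 90/600 = 15% over the whole period. The gap is 60 points, or 60/42 = 1.4 points per switched patient. At 4 h it is 210/240 = 87.5% against 210/600 = 35%, a gap of 52.5 points, or 1.25 per patient.

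**Comparison with a control patient.** Take a propofol patient with the same first 2 h whose infusion continues to 600 min. If in target for 0 to 50% of the remaining 480 min, this patient scores 108/600 = 18% to (108 + 240)/600 = 58%. The switched remimazolam patient scores 90%.

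**The case against.** The strongest reply is that the term study drug is not defined. Both arm sections use the same sentence about giving it, propofol is one of the two randomised drugs, and the rescue infusion has the same rate range as control maintenance. If rescue propofol counts as study drug infusion, time after the switch stays in the denominator and out of the numerator, and the problem disappears. This reading is possible. It is the less natural one, because the article labels that infusion rescue therapy and the endpoint sets rescue apart from study drug. The full protocol is not shown and may settle the point. The article, however, does state a denominator, so this is not simply detail left out.

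It can also be said that scoring patients only while on assigned drug is a legitimate choice, and that rescue is reported separately. But the numerator already counts rescue against remimazolam, so dropping its heaviest form does not fit the endpoint's own logic. A separate secondary incidence does not correct the primary comparison.

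Four stronger readings are tempting, and the documents do not support them:

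- *Switching costs the experimental arm almost nothing.* Not for early switches. Under the 12-min assumption a switch at 1 h scores 80%, and one at 20 min scores 8/20 = 40%; both are below the 82% assumed for propofol.
- *A failing control patient can never leave the denominator.* The bar on other sedatives is the same in both arms, yet rescue is allowed in one despite it. If propofol were stopped for failure, its clock would stop too. What the text shows is only that a rescue switch is defined for one arm.
- *The bias is known to be large.* A switch needs the maximum dose, more than 3 min out of range and three failed loading doses, and patients who need deep sedation are excluded. There may be few switches or none. RASS is recorded every 30 min, so 12 min is finer than the record.
- *The shift converts into a particular type I error, power or new sample size.* That would apply binomial variance to a mean of per-patient time proportions, whose standard deviation is not given.

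**Conclusion.** The point holds on the plain reading of the endpoint and rescue sections: a patient who fails remimazolam and is switched is scored only on the time before the switch. Relative to whole-period scoring the effect can only favour remimazolam. That direction follows from the definitions and needs no assumed number.

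The size does rest on assumptions. With 600 min of sedation and 12 min out of target before the switch, each switched patient among 42 adds about 0.5 points (at 8 h) to 1.7 points (at 1 to 2 h), against a 10-point margin. With no switches, or a few late ones, the effect is negligible. With several early ones it is material: four at 2 h add 6.9 points.

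This should be corrected before analysis. The trial is described as open-label, and a primary denominator that can be read two ways should not be settled once results are visible. Confidence is moderate, because study drug is undefined and the switch rate is unknown.

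**What to change.** In Primary Outcomes, define one denominator for both arms: the time from the start of study drug to the end of all sedative infusion, including any rescue propofol infusion. Keep the numerator as it stands, so that all time after a switch counts as not satisfactory. Report the number of patients switched and the time of each switch. If the sponsor always meant rescue propofol to count as study drug infusion, one sentence saying so has the same effect.

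The cost is a change of one phrase. No new data are needed: time after the switch scores zero, and the Data Management section already lists "usage and drip speed of sedatives and analgesics" among the data collected.

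The drawback is power. If the assumed 92% made no allowance for switched patients, the experimental rate will be somewhat lower. Two of 42 switched at 2 h would take it to 92 − 3.4 = 88.6%. How much power that costs cannot be stated without the standard deviation of the per-patient time proportion and a switch rate. The sponsor should set out both as planning assumptions.
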